#### Biomechanical variable definitions

The following operational definitions apply to the biomechanical variables presented in Table 1:
-Center of pressure (COP) sway area (cm^2^): Total area encompassed by the COP trajectory during the assessment period, calculated using a 95% confidence ellipse method.-COP velocity (cm/s): Mean velocity of COP displacement, calculated as total COP path length divided by trial duration.-Root mean square (RMS) of COP sway (cm): A measure of COP variability representing the average deviation of the COP from its mean position throughout the trial.-Trunk-pelvis coupling angle (°): The relative phase angle between trunk and pelvis segments during turning movements, calculated using vector coding analysis to quantify intersegmental coordination timing and magnitude.-Co-contraction index (unitless): The ratio of antagonist to agonist muscle activation during specified movement phases, with higher values indicating greater simultaneous activation and potentially less efficient motor control.-Time to peak vertical ground reaction force (ms): Duration from movement onset (defined as the first rise in vertical force exceeding 5% of body weight) to the maximum vertical ground reaction force during the sit-to-stand transition.

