#### Secondary (exploratory) outcomes: biomechanical variables

While static balance (37–40) contributes to standing/seating stability and function, the dynamic and reactive components (38–41) are crucial for children to engage in life activities such as navigating through busy school hallways. Secondary, exploratory biomechanical outcome measures organized by assessment task are outlined in Table 1.

**Table 1 T1:** Detail of secondary, biomechanical outcome measures.

Approach	Variable	Level of outcome
Static Balance: NIH Toolbox Standing Balance Test		
Kinetics	• COP sway area (cm^2^) and velocity (m/s) • RMS of COP sway (cm)	• Primary • Primary
Electromyography	• Thigh co-contraction* (Quads:Biceps Fem) • Leg co-contraction (Gastroc:Tibialis Ant) • Peak activity (%movement cycle) of distal vs. proximal muscles	• Secondary • Secondary • Secondary
Dynamic Balance: Five-Times-Sit-to-Stand Test and Modified Timed Up and Go		
Kinematics	• Trunk-pelvis coupling (°) during turning step of mTUG	• Secondary
Kinetics	• Time (ms) to reach peak vGRF (5TSTS) • COP sway area (cm^2^) (5TSTS, mTUG turning step) and velocity (m/s) (5TSTS) • RMS of COP sway (cm) (5TSTS, mTUG turning step)	• Secondary • Primary (5TSTS) • Primary (5TSTS)
Electromyography	• Thigh co-contraction* (Quads:Biceps Fem) • Leg co-contraction (Gastroc:Tibialis Ant)	• Secondary • Secondary
Gait: 10-Meter Walk Test, Self-Selected Speed and Fast Pace		
Kinematics	• Hip posture (°) at terminal stance • Trunk posture (°) at initial contact	• Secondary • Secondary
Electromyography	Peak, mean, and duration (%Gait Cycle) of: • Gastrocnemius, Tibialis anterior • Biceps femoris, Vastus Lateralis • Gluteus Maximus	• Secondary • Secondary • Secondary
Spatiotemporal Characteristics	• Speed (m/s) • Single limb stance time (%Gait Cycle)	• Secondary • Secondary

5TSTS, five-times-sit-to-stand test; COP, center of pressure; Gastroc:Tibialis Ant, ratio of gastrocnemius to tibialis anterior; mTUG, modified timed up and go; Quads:Biceps Fem, ratio of quadriceps femoris to biceps femoris; RMS, root mean square; vGRF, vertical ground reaction force.

* Unitless.

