### Assessment protocols

Biomechanical assessments will be performed at three timepoints (Figure 1): baseline (3 months prior to intervention), pre-intervention (same day as child receives the individually adapted PMD), and post-intervention (3 months after receiving the individually adapted PMD). Reflective markers will be placed on anatomical landmarks according to a modified Plug-in-Gait model for full-body kinematic tracking. Surface EMG electrodes will be placed bilaterally on tibialis anterior, medial gastrocnemius, rectus femoris, biceps femoris, and gluteus maximus, following SENIAM guidelines.

The following standardized protocols will be administered:

***Static Balance***: NIH Toolbox Standing Balance Test (42). Participants will stand barefoot on a single force platform in a standardized stance (feet hip-width apart, arms at sides) for up to 50 s with eyes open, followed by 50 s with eyes closed. Three trials will be collected for each condition, with rest periods between trials as needed. These two conditions will also be performed with children standing on an unstable surface (Airex®). Tandem stance will also be attempted per protocol.

***Dynamic Balance***: Five-Times-Sit-to-Stand Test (5TSTS) (43) and Modified Timed Up and Go (mTUG) (44). For the FTSTS, participants will be seated on a height-adjustable bench (allowing for 90° of hip and knee flexion) with feet resting on the force plate. Participants will be instructed to stand up and sit down five times as quickly as possible with arms crossed over the chest. Three trials will be collected with rest periods as needed. Hand support will be provided for those who cannot independently rise from the bench. For the mTUG, participants will rise from the seated position, walk 3 meters at a self-selected pace, turn 180°, return to the chair, and sit down. The turning period of the task will be captured on the force plate. Three trials will be collected with adequate rest between trials. Hand-held support will also be provided for those who are unable to walk independently.

***Gait***: 10-Meter Walk Test (45). Participants will walk along the instrumented walkway at self-selected comfortable speed and at fast pace. Three trials will be collected for each speed condition, with rest periods as needed. Hand-held support will be provided for those who are unable to walk independently.

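### Static sway area and RMS grow with how long the child stands, and 5TSTS sway moves with speed and hand support, so pre-post changes in these outcomes mix that with balance

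*Protocol article*

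**What the plan says.** Under Biomechanical variable definitions, the Protocol article gives sway area as the "Total area encompassed by the COP trajectory during the assessment period", by a 95% ellipse. RMS is the "average deviation of the COP from its mean position throughout the trial", and velocity is "calculated as total COP path length divided by trial duration".

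Under Assessment protocols, static stance lasts "for up to 50 s with eyes open, followed by 50 s with eyes closed", with three trials per condition and the same two conditions repeated on foam. In the 5TSTS the child is told to "stand up and sit down five times as quickly as possible with arms crossed over the chest", and "Hand support will be provided for those who cannot independently rise from the bench".

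Table 1 marks COP area, velocity and RMS as Primary for static balance and for 5TSTS, and marks nothing else so, although the whole table is headed secondary and exploratory. Statistical treatment reports pre-post effect sizes with confidence intervals and no hypothesis tests, and uses the SDs to guide the size of a future RCT. An SD that permits sample-size estimation is also one of the progression criteria.

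**The concern.** Sway is autocorrelated: slow drift that a short record misses shows up in a longer one. Ellipse area and RMS about the trial mean therefore increase with record length even when balance is the same. The static test sets a ceiling but no minimum and no shared window, so record length is free to follow ability. The participants are GMFCS level III children who may qualify by standing with assistance, and they are tested eyes closed and on foam, so short holds are plausible. Longer standing is also a gain that the intervention might produce.

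The 5TSTS has two further couplings. Dividing path by duration in a speed test makes velocity depend on speed. Support given by ability can change the COP trace for reasons other than balance.

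At stake are the pre-post effect sizes and the variability of change, which are meant to guide outcome selection and the size of the next trial. The waitlist comparison does not remove an artefact that appears when ability changes between pre and post. Multiple imputation does not address a trial that was short but recorded.

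**Working it through.** **Inputs.** From the article: the 50 s ceiling, the three definitions, the support rule and n = 10. The article gives no hold times, sway time constants or support effects, so those below are assumptions. There is no figure in the article to reproduce.

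**1. Why length matters.** For a stationary signal with variance σ² and time constant τ, the expected variance about the trial's own mean over T seconds is σ²·f(T), with f(T) = 1 − 2(τ/T)[1 − (τ/T)(1 − e^(−T/τ))]. For τ = 5 s:
- f(15) = 1 − 0.667 × (1 − 0.333 × 0.950) = 0.544
- f(50) = 1 − 0.2 × (1 − 0.1 × 1.000) = 0.820
- variance ratio 0.820/0.544 = 1.51; RMS ratio √1.51 = 1.23

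**2. Size under a mixed model.** Sway was simulated as a fast plus a slow component (slow time constant 3-20 s, slow share 50-70%, 3000 runs). Area over 15 s was 67-83% of area over 50 s, and RMS was 82-93%. Going from 15 s to 50 s therefore multiplies area by 1/0.83 to 1/0.67 = 1.20 to 1.49, and RMS by 1/0.93 to 1/0.82 = 1.08 to 1.22.

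**3. Adding a true gain.** A fall in sway amplitude scales RMS directly and area by its square.

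| True fall in amplitude | Observed area ratio, post/pre | Observed RMS ratio, post/pre |
|---|---|---|
| 10% | 0.81 × 1.20-1.49 = 0.97-1.21 | 0.90 × 1.08-1.22 = 0.97-1.10 |
| 20% | 0.64 × 1.20-1.49 = 0.77-0.95 | 0.80 × 1.08-1.22 = 0.86-0.98 |

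A 20% gain, which should cut area by 36%, shows a cut of 5-23%: masked, not reversed. A 10% gain is reversed over part of the range.

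**4. Sensitivity to the sway model.** If all sway is one process (15 s then 50 s, mean of three trials), a 10% fall gives simulated area ratios of 0.93, 1.36, 1.71 and 2.08 for τ = 1, 5, 10 and 20 s. A 20% fall gives 0.73, 1.08, 1.36 and 1.65. The chance that a child with a true 10% gain scores worse on area is 0.33-0.98. With a 15 s window at both visits it is 0.15-0.28. Static velocity behaves correctly throughout (ratio 0.90 for a 10% fall).

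**5. 5TSTS velocity.** The same path in 25% less time gives 1/0.75 = 1.33 times the velocity; 20 s instead of 30 s gives 30/20 = 1.50.

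**6. 5TSTS support.** Suppose support cuts amplitude by a fraction h, and a child with a 20% true gain no longer needs it. The area ratio is (0.80/(1 − h))²: 0.79 for h = 0.1, 1.31 for h = 0.3 and 2.56 for h = 0.5. For the group, suppose 3 of 10 children drop support that had halved their area, with equal unsupported areas and no true change. The pre mean is 0.7 + 0.3 × 0.5 = 0.85 of the post mean, a rise of 1/0.85 − 1 = 18%. For area cuts of 25% and 60% the rise is 8% and 22%.

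**The case against.** **This is a condensed article.** Windows, early-stop rules and support logs may sit in the full protocol or the processing scripts, and their absence here is no finding. That carries weight for support: the text ties it to ability and is silent on consistency across visits, so a change between visits is an inference. It carries less for the static measures. The article states the definitions, and as written they take the whole trial or assessment period. Elsewhere it does restrict variables to a phase: co-contraction (Data processing) and time to peak vertical force. That the 5TSTS COP record includes seated phases is likewise a reading of the definitions, not a statement in them.

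**The artefact does not reach every Primary COP outcome.** This stands. Static velocity is time-normalised, and static stance has no stated hand support. The mTUG allows hand-held support, but its COP variables are not marked Primary.

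**A reader might infer that improving children will generally score as worse.** The documents do not support that. They give no hold times, 15 s to 50 s is a large assumed change, and under the mixed model a 20% gain still reads as a gain. Reversal at 20% needs the single-process model with long time constants. Nor does any passage say that higher COP velocity in a fast repeated-rise test is worse.

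**A reader might also infer that the SDs are inflated.** This is not shown. Short holds or support among the weakest children could compress the spread at a single visit.

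**The outcomes are exploratory**, with feasibility primary and no testing. This stands and lowers the severity.

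**Conclusion.** The concern holds in a limited form. Static area and RMS, as defined, confound sway with hold time: about 20-49% on area and 8-22% on RMS for a move from 15 s to 50 s, given the assumed two-component model. The consequence is a masked gain or, for small true gains, apparent worsening. In the 5TSTS, COP changes mix balance with speed and, if support changes between visits, with support. The size of the support effect is unknown and rests wholly on assumption. The pre-post effect sizes and change-score SDs are distorted; the direction of any effect on single-visit SDs is not established. The plan should be corrected, but the feasibility conclusions on recruitment, retention and adherence are untouched.

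**What to change.** **Static stance.** For each child and condition, compute area and RMS on one common window at baseline, pre and post: the shortest valid hold across the three visits, with validity defined in advance. Report hold time (0-50 s) as its own outcome. Velocity can stay as it is.

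**5TSTS.** Record the support level at every visit and compare COP only between trials with the same support. Restrict COP to a defined rising or standing phase, as Data processing already does for co-contraction. A rule requiring nearly full body weight on the plate would not serve, because it could discard the supported trials that the comparison needs. Report 5TSTS time and COP path per repetition beside velocity.

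**Cost.** The static change is a script change. The support record is a data-sheet item, but it must be made at testing because it cannot be recovered later. Shorter windows discard some data, and a strict minimum hold would remove the weakest of only ten children. A child whose support changes needs a matched-support trial or drops out of that comparison.

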### Assessment procedures and outcome measures

The primary aim of this study is to determine whether a full-scale RCT is feasible. The feasibility of a future RCT will be determined using the following progression criteria:
-Recruitment Feasibility: At least 70% of eligible participants consent to enroll within the recruitment period.-Retention Rate: At least 80% of participants complete all study visits and assessments.-Adherence: Participants use the stand-on PMD for an average of at least 20 min per day based on device tracking.-Variability of Primary Outcomes: Standard deviation of biomechanical outcomes should allow for a sample size estimation in a full-scale trial.

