### Data processing

Kinematic and kinetic data will be processed using Vicon Nexus 2.0 software for marker labeling, gap filling, and initial data quality checks. Subsequently, biomechanical calculations including hip, knee, and ankle joint angles, as well as trunk and pelvis segment angles, kinetic variables, and lower extremity muscle activity patterns will be performed using custom scripts developed in Python (version 3.11) and MATLAB (R2025a, MathWorks, Natick, MA). Whole-body coordination analysis, including trunk-pelvis coupling using vector coding methods, will be performed using *vailá*, an open-source multimodal motion capture toolbox (46). Raw sEMG signals will be band-pass filtered (fourth-order Butterworth), full-wave rectified, and smoothed using a root-mean-square algorithm with a 50-ms moving window. EMG amplitude will be normalized to peak activity achieved during static standing for each muscle. Co-contraction indices will be calculated as the ratio of flexor to extensor muscles during specified movement phases (e.g., rising from the seat during FTSTS).

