### Statistical treatment

Due to the pilot nature of this study, descriptive statistics will be used to summarize feasibility outcomes, including recruitment, adherence, and retention rates. Variability in biomechanical measures will be estimated using means, standard deviations, and confidence intervals to guide sample size calculations for a future RCT. Given the small sample size, formal hypothesis testing will not be conducted. Preliminary pre-post comparisons of biomechanical outcomes will be reported using effect sizes (e.g., Cohen's d) and confidence intervals. Statistical analyzes will be performed with IBM SPSS Statistics version 28.0 (IBM Co., Armonk, NY, USA).

An external biostatistician will be contracted to perform all statistical treatments and control for any potential observer bias. The biostatistician will also manage the dataset to adjust for any missing data. We envision the use of multiple imputation where necessary, with assumption that the mechanism of missing data points was missed at random.

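### Trunk-pelvis coupling is labelled as one quantity and computed as another, and the stated means, SDs and Cohen's d can fail for a directional angle

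*Protocol article*

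**What the plan says.** All references are to the protocol article.

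- **Table 1** lists "Trunk-pelvis coupling (°) during turning step of mTUG" under dynamic balance kinematics, at the level Secondary.
- **Biomechanical variable definitions** gives its operational meaning: "The relative phase angle between trunk and pelvis segments during turning movements, calculated using vector coding analysis".
- **Data processing** assigns the computation to an open-source toolbox: "Whole-body coordination analysis, including trunk-pelvis coupling using vector coding methods, will be performed using" that toolbox.
- **Statistical treatment** gives the summaries for all biomechanical measures together: "Variability in biomechanical measures will be estimated using means, standard deviations, and confidence intervals to guide sample size calculations for a future RCT". For change over the intervention: "Preliminary pre-post comparisons of biomechanical outcomes will be reported using effect sizes (e.g., Cohen's d) and confidence intervals". The software named is SPSS, and there is no formal hypothesis testing.

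The article states no range for the angle, no sign or turn-direction convention, and no separate summary for a directional variable.

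**The concern.** There are two linked problems.

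**The definition.** Vector coding takes the direction of the line joining successive points on a plot of one segment angle against the other. Relative phase is the difference between two phase angles. Both are in degrees, but the same movement has different values on the two scales. The participant-level data are to be deposited publicly, so someone who takes the label at its word would misread the coordination pattern.

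**The summary.** A coupling angle is a direction. Arithmetic means and SDs treat 350° and 10° as 340° apart, when they are 20° apart. They also treat the same in-phase pattern in a left and a right turn as opposite values. At stake are the reported pattern, its change after the intervention, and an SD that the article wants for planning the next trial. Trunk-pelvis coupling is the only intersegmental coordination measure in Table 1. The other two outcomes in degrees, hip and trunk posture during gait, are postures at one gait event and should not come near a wrap.

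**Working it through.** The plan gives no mean, SD or sample size for this outcome, so there is no figure to reproduce. What follows checks the definition, then shows when the stated summaries fail.

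**Inputs from the article:** angle in degrees, computed by vector coding; 10 children; a 180° turn in the modified Timed Up and Go; summaries by mean, SD and, as an example, Cohen's d.

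**Assumptions:** angles kept on 0–360°; true between-child SD of 10°, 20° or 26°; various centres. The article supports none of these values, so a range is shown.

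**1. The two quantities differ.** The coupling angle is atan2(Δpelvis, Δtrunk).
- Equal increments in the same direction give atan2(1, 1) = 45° for one turn direction and atan2(−1, −1) = 225° for the other.
- Equal and opposite increments give 135° or 315° (anti-phase).
- Relative phase for the in-phase case is 0°.

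**2. Wrap error.** Two values: (350 + 10)/2 = 180°, whereas the mean direction is 0°.

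For X normal with centre μ and SD σ, recorded on 0–360°, a value below 0 has 360 added. With p = Φ(−μ/σ) and φ the standard normal density:

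linear variance = σ² + 360²·p(1 − p) − 2·360·σ·φ(μ/σ)

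- μ = 45, σ = 20: p = 0.0122, φ(2.25) = 0.0317. Variance ≈ 400 + 1,565 − 457 = 1,508, so SD ≈ 38.8°.
- μ = 45, σ = 26: p = 0.0417, φ(1.731) = 0.0892. Variance ≈ 676 + 5,184 − 1,670 = 4,190, so SD ≈ 64.7°. Von Mises simulations with about the same spread gave 63–66°.

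Large-sample linear mean and SD:

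| Centre | True SD 10° | True SD 20° | True SD 26° |
|---|---|---|---|
| 0° | 180°, 172° | 180°, 165° | 180°, 160° |
| 45° | 45°, 10° | 49°, 39° | 60°, 65° |
| 90° | 90°, 10° | 90°, 20° | 90°, 26° |
| 180° | 180°, 10° | 180°, 20° | 180°, 26° |
| 225° | 225°, 10° | 225°, 20° | 225°, 26° |

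**3. At n = 10** the inflation comes in jumps. With centre 45° and true SD 20°, the chance that at least one of ten values crosses is 1 − (1 − 0.0122)¹⁰ ≈ 0.12. In 3,000 simulated samples the sample SD averaged 28.6° and exceeded twice the true SD in 12% of samples. With a true SD of 10° it averaged 9.7°, so there was no harm.

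**4. Mixed turn directions.** Take 35, 40, 45, 50, 55 and 215, 220, 225, 230, 235, all in-phase.
- Linear mean = (225 + 1,125)/10 = 135°, the anti-phase pattern; SD = 95°.
- Circular mean: the resultant length is 0, so it is undefined.
- Axial mean (double the angles, average, halve): 45°, with an angular SD of 7.1°.

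**5. Change.** A true shift from 350° to 10° with SD 5° is +20°, so d = 20/5 = 4. The linear calculation gives (10 − 350)/5 = −68.

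**The case against.** The strongest reply is that the Statistical treatment section is one generic paragraph in a condensed article. Cohen's d is only an example, the word linear never appears, and the angle range and averaging rule may sit in the toolbox, the full protocol or the code. Silence on that level of detail is not a fault. This stands in part: the 0–360° scale is assumed, and the toolbox may average circularly within a trial. It does not clear the text, because the article states a rule covering all biomechanical measures, and reading means, SDs and Cohen's d as circular statistics is strained.

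A second reply is that the reader can tell which method is meant, since vector coding is named in two sections. That is fair, and it makes the label an easy correction. It remains a wrong operational definition.

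A third reply concerns size. In a 180° turn, trunk and pelvis rotate the same way overall, which points to values near 45° or 225° and not near 0°. There the harm is none to moderate unless turn directions are mixed. This stands.

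Two stronger readings are tempting:
- **That the SD will be grossly inflated.** Ten invented angles placed on the wrap give a linear SD of 183.6° against a circular 6.5°. For an assumed 10° difference (two-sided 5%, 80% power) that means 5,295 against 7 children per arm. Nothing in the article says the angles lie there.
- **That the progression decision is compromised.** The criterion reads "Standard deviation of biomechanical outcomes should allow for a sample size estimation in a full-scale trial", but its title confines it to primary outcomes, and Table 1 ranks this variable as Secondary.

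**Conclusion.** The point holds in a limited form. The definition joins two different quantities; that follows from the text alone. The stated summaries are not valid for a directional variable when values cross the wrap or turn directions are mixed. How much this matters depends on where the angles fall and on the assumed 0–360° scale. It ranges from no error, through a linear SD of roughly two to two and a half times the true one in large samples (centre 45°, true SD 20–26°), to a meaningless mean and SD near 0°. With turns in both directions the mean can name the opposite coordination pattern.

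The reach is one exploratory secondary outcome, with no hypothesis test. The practical loss is a misleading description and an unreliable SD for planning the later trial. The progression criterion on primary outcomes, which are all centre-of-pressure measures, is untouched.

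**What to change.** **Biomechanical variable definitions:** remove the reference to relative phase, define the outcome as the vector-coding coupling angle, and state its range. Add a turn-direction convention (for example, reverse the sign of both segment rotations for one turn direction), or specify axial, doubled-angle averaging. A plain circular mean without one of these is not enough: in the mixed-turn example it is undefined.

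**Statistical treatment:** exempt this variable from the linear mean, SD and Cohen's d. Report the circular (or axial) mean and angular SD, within and across children. Report change as the angular difference wrapped to −180° to +180° (−90° to +90° if axial), with a confidence interval, for instance by bootstrap. Frequencies of coordination patterns would be an acceptable alternative.

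**Cost:** two or three sentences and a few lines in the Python or MATLAB scripts already planned. No new data, visits or participants.
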